### Procedure

After providing consent, all participants were instructed on how to use the pedometer or the app, respectively, and how to share the number of tracked steps via the Web-based platform of the health insurance company. The Web-based platform supported devices of the brands Garmin, Jawbone, and Fitbit, all commonly known manufacturers of wearables and fitness technology. Alternatively, participants could use the Fitbit app that is available for selected mobile phones. A systematic review has confirmed the validity of commercial pedometers [62], and recent studies provide evidence for the accuracy of smartphone apps for tracking physical activity data [63]. Owning an eligible tracking device (pedometer or smartphone app) was thus required for participation. Participants not owning an eligible pedometer were entitled to a 20% discount on a compatible device. All participants could use the Web-based platform any time to gain insight into their physical activity data as well as their degree of achievement with regard to their goal of 10,000 steps per day. In the charitable condition, participants could also log in to choose a particular charitable organization from a predefined list and set the proportion of money they want to donate. Participants were asked to set this proportion once at the beginning and once before the end of the PHI.

During the course of the intervention, participants received short informational texts in order to maintain motivation for daily physical activity (eg, “If you are going by bus consider getting off two stops prior to your destination to reach your goal of 10,000 steps per day”). Those texts were based on information material and recommendations for health effective daily activity provided by the Federal Bureau of Sports as well as on recommendations for increasing step count in everyday life [7] and on the Compendium of Physical Activities 3 [64]. Additionally, participants received a status mail on a monthly basis that informs them once again about their target achievement and the respective amount of money saved or donated during the past month. This mail also contained further season-based tips on how to increase the daily step count (eg, recommending free geocaching apps or websites for summer days or popular snowshoeing trails during winter). The content of the monthly status mails was developed in cooperation with the insurance company.

At any time, participants were able to opt out of the PHI and request the deletion of all submitted data without giving reasons. In order to prevent high dropout rates that have been observed in past pedometer-based interventions [13], no bonus will be granted for past achievements if the participant decides to opt out of the PHI.

### Data Collection and Variables

Data for analysis is partly collected by submission of information by the participants via the Web-based platform of the insurance company and partly by administering a Web-based questionnaire at 2 different points in time (T_1_ and T_2_) over the course of the intervention. After participants registered their pedometer or smartphone at the Web-based platform of the insurance company, the number of steps were synchronized automatically with the Web-based platform each day at midnight. However, participants could choose to deactivate automatic synchronization and enter their step count manually on the Web-based platform. Days where no step data is available (eg, because the pedometer was not worn or not charged) will be treated as missing data. The first measurement (T_1_) is set at the beginning of the PHI for all groups, whereas the second measurement (T_2_) is set at the end of the intervention for the experimental groups and after the first half of the intervention for the control group before they received financial incentives. Additional data, such as age, gender, or participants’ health service billings, were provided by the insurance company. To guarantee appropriate response rates, participants received additional $5 for each time they completed the questionnaire resulting in an additional bonus of $10. See Figure 1 for an overview of the study design.

The following variables were measured for analysis: the participation rate represents the primary outcome and is measured by calculating the participation rate in total and for the different groups, respectively. Participation rate is defined as the proportion of active participants that is participants that shared their data with the Web-based platform of the insurance company at least once. Secondary outcomes are continued use of the pedometer, performance of the participants, and health condition. The number of days at which participants share their step count with their health insurance company is used as an indicator of the continued use of the pedometer. The number of steps and the amount of money saved or donated indicate the performance of the participants. Apart from the number of steps, physical activity was also assessed by questionnaire measures namely hours of moderate to vigorous physical activity and hours of walking per week at T_1_ and T_2_ (based on the International Physical Activity Questionnaire [65,66]), walking on the way to work, physical activity at work, and during spare time at T_1_ and T_2_. The proportion of money saved versus donated (at T_1_ and T_2_) is further used to evaluate the charitable incentive condition. We use health perception at T_1_ and T_2_ (“How would you rate your overall health status?”) [67-69] and improvement of health perception due to the intervention at T_2_ (eg, “In general, my health improved due to the prevention program”) [67-69] as subjective measures and service billing with the health insurance company (ie, amount of money repaid by the insurance company per participant) after completion of the prevention program and 1 year later as objective measures in order to assess effects on participants’ health condition. Unless otherwise indicated, a 7-point Likert scale, from strongly disagree (1) to strongly agree (7), will be used for items requiring a response scale.

To exclude possible confounding influences, we will measure the following control variables: sociodemographic variables (age, gender, education, income, and nationality [67,70,71]) measured at T_1_, technology readiness [72] measured at T_1_, possession of pedometers and other self-tracking tools at T_1_, pedometer brand measured at T_1_, number of persons living in the participants’ household at T_2_, living environment at T_1_ (city center, outer city, village, countryside), amount of billing services preceding the prevention program at T_1_, exchange with other participants of the prevention program at T_2_, participation of a family member or friend at T_1_, and observation of media coverage of the prevention program and possible impact on participants’ physical activity at T_2_.

Additional variables were measured to better understand the participants behaviour. These variables are participants’ perception of the Web-based platform, perception of the insurance company (eg, perceived social responsibility), customer loyalty, participants’ willingness to share data with their insurance company, willingness to donate (in the charitable incentive group), reasons for participating and not participating, reasons for opting out, and improvement suggestions to the program.

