## Methods

### Experimental Groups

Over the course of the PHI, participants had to achieve a fixed level of physical activity each month that was tracked using a commercial pedometer device or app that automatically counts the number of steps when walking. In order for the PHI to be effective, 150 minutes of moderate physical activity are recommended [54-56], which on average translates to a goal of 10,000 steps per day [7,57,58]. Upon achieving that goal, participants received a monthly incentive depending on the EG they were assigned to. Textbox 1 shows descriptions of the groups.

Experimental group descriptions.Financial incentive (EG1)• In this condition, participants were entitled to a $10 reward each month they reached an average of 10,000 steps per day or more. Participants achieving more than 7500 steps per day were granted $5 in order to prevent frustration [7]. The minimum recommendation for daily physical activity is approximately 7500 steps per day [57,58].Charitable incentive (EG2)• Here, participants received the same rewards as in the financial incentive condition. However, participants had to decide whether a certain proportion of the money should be donated to a charitable organization chosen from a predefined list (proportions varied from 0% to 100% in steps of 5% with 50% being the default).Control group (CG/EG1)• Participants of the control group received no incentives over the first 3 months of the PHI. Due to the practical setting of our study, ethical consent and fair treatment of all participants is of highest relevance. Participants in the control group were therefore entitled to a $20 reward each month they averaged over 10,000 steps per day and a $10 reward each month they averaged over 7500 steps per day over the fourth to sixth month of the intervention. To avoid anticipatory effects on the participation rate, participants in the control group were not informed of the opportunity to receive financial rewards during the second half of the PHI.Thus, all participants had the chance to earn a maximum of $60 that is paid at the end of the PHI.

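### Control moves to double rewards at month 4, so money earned and later billings cannot show incentive versus none, and steps and days shared need a stated comparison window

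*Protocol article*

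**What the plan says.** The reward schedule is in the Experimental Groups section of the protocol article. For control in the first half: "Participants of the control group received no incentives over the first 3 months of the PHI". For the second half: "Participants in the control group were therefore entitled to a $20 reward each month they averaged over 10,000 steps per day", with a $10 lower tier above 7500 steps, and this applies "over the fourth to sixth month of the intervention". In the financial group, "participants were entitled to a $10 reward each month they reached an average of 10,000 steps per day or more", with $5 for the lower tier, throughout the six months. The charitable group has the same amounts. The section adds that "all participants had the chance to earn a maximum of $60 that is paid at the end of the PHI".

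Data Collection and Variables lists the secondary outcomes. Continued use is the number of days on which steps are shared. For performance, "The number of steps and the amount of money saved or donated indicate the performance of the participants". Health service billings are taken "after completion of the prevention program and 1 year later as objective measures". No comparison window is attached to steps, days or money. For the questionnaires, the same section places control's second measurement at the end of the first half, before its rewards begin.

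Data Analysis plans a mixed-effects model with step counts nested in participants, and Baseline Characteristics adds group-specific intercepts. Neither mentions a term for the change in control's incentive. Strengths and Limitations discusses only the different timing of the second questionnaire.

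**The concern.** The stated objective is the effect of incentives on acceptance and adherence. Acceptance is measured by participation. Adherence and performance are measured over a program during which control stops being an unpaid comparator. From month 4, an experimental-versus-control contrast sets a single reward against a double one. After month 6, every group has been offered the same maximum.

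Two outcomes are affected by how they are defined. Money depends on the payment schedule as well as on behaviour, and the schedule differs by group and period. Billings are observed only after control has been paid. For steps and days shared the difficulty is conditional. If the six months are pooled, the estimate mixes two different comparisons, and a weak result could be read as a weak incentive effect. The authors protected the questionnaire outcomes from the switch, but the article does not extend that protection to the other outcomes.

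**Working it through.** **1. Reproduce the plan's figure.** The inputs are the monthly rewards in Experimental Groups.

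- Experimental groups, upper tier: 6 × $10 = $60.
- Control, upper tier: 3 × $0 + 3 × $20 = $60.
- Lower tier: 6 × $5 = $30 and 3 × $10 = $30.

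The $60 maximum is confirmed. It is equal across groups only because control's rate is doubled for half of the time.

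**2. Money as a performance measure.** Apply the schedules to identical behaviour.

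| Months reaching 10,000 steps | Experimental | Control |
|---|---|---|
| 1 to 6 | 6 × $10 = $60 | 3 × $20 = $60 |
| 1 to 3 only | 3 × $10 = $30 | 3 × $0 = $0 |
| 4 to 6 only | 3 × $10 = $30 | 3 × $20 = $60 |

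The same behaviour scores differently in two of the three rows, and in opposite directions. Choosing a window does not repair this: in months 1 to 3 control scores $0 whatever it does, and in months 4 to 6 it scores double.

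**3. Billings.** Control's rewards run in months 4 to 6. Both billing measurements fall after the program. At neither time is there a group that was never offered the incentive, so the contrast is six months at the single rate against three unpaid months followed by three at the double rate.

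**4. Steps and days shared, if six months were pooled.** Assume that the incentive shifts the experimental groups by d in both halves, that control shifts by 0 in months 1 to 3 and by λd in months 4 to 6, and that the halves have equal weight. The six-month contrast is then

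½·d + ½·(d − λd) = d·(1 − λ/2).

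The documents give no value for λ, no step effect and no SD, so a range is shown. For power, take a contrast with 80% power for the full effect at two-sided 5% and an unchanged standard error (all assumed). With f = 1 − λ/2, power is Φ(f × (1.960 + 0.842) − 1.960).

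| λ | Effect retained | Power |
|---|---|---|
| 0 | 100% | 80% |
| 0.5 | 75% | 56% |
| 1 | 50% | 29% |
| 1.5 | 25% | 10% |
| 2 | 0% | 2.5% |

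At λ = 1, control responds to its later reward exactly as the experimental groups respond to theirs.

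**5. Months 1 to 3 alone.** The comparison is $10 against $0 per month and the full d is estimated (fraction 1.0). Precision falls because fewer days are used; the documents do not allow that loss to be quantified.

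**The case against.** The strongest reply is that the article never says control is treated as unpaid for six months. A reader might infer from the list of outcomes that steps, days, money and billings will all be compared as if control had stayed unincentivised. The text does not support that. It names variables and defines no six-month contrast. The label CG/EG1 and the month-3 questionnaire for control show that the switch was recognised.

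This answer stands for steps and days shared. Steps are normally synchronised daily and enter the planned model as repeated measures, so a separate analysis of months 1 to 3 is possible and not excluded. Time windows are also commonly left to a fuller analysis plan, which is not shown.

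It does not dispose of money and billings. The article does not explicitly schedule an experimental-versus-control test of either. But it names money as an indicator of performance and billings as an objective measure of effects on health, and fixes when billings are taken. No later choice of window turns either into a measure of incentive versus none.

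It is also fair that the dilution figures are hypothetical, and that the article's stated main focus, participation, is untouched. Control invitees were not told of the later rewards, and participation requires only that data be shared once.

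**Conclusion.** The point holds in a limited form, at moderate severity and for secondary outcomes only.

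- **Money:** not a valid performance measure between experimental and control groups. Identical behaviour can differ by $30 in either direction. This follows from the stated schedule without further assumptions.
- **Billings:** an experimental-versus-control contrast measures immediate against delayed incentive. This follows from the stated timing.
- **Steps and days shared:** only months 1 to 3 compare incentive with none, and the article does not say that this window will be used. A pooled six-month contrast would keep 50% of the effect if control responded equally, with a range of 100% to 0% for a response of 0 to 2 times the experimental effect. It is not established that a pooled contrast is planned.

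It would go too far to conclude that the trial cannot estimate the incentive effect on steps or days, since the daily data allow it. The participation-rate outcome and the comparison of financial with charitable incentive, which share one schedule, are not affected.

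**What to change.** Add to Data Collection and Variables and to Data Analysis:

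- **Steps and days shared.** For experimental-versus-control comparisons, estimate the incentive effect from months 1 to 3, either by restricting to those months or by adding a group-by-phase term to the planned mixed model. Report months 4 to 6 separately, with control described as receiving a delayed, double incentive.
- **Money.** Replace it in these comparisons by the number of months in which the participant reaches 7500 and 10,000 steps, analysed within the same two phases. Keep money as a descriptive measure and for comparing the financial with the charitable group.
- **Billings.** State that experimental-versus-control contrasts are interpreted as immediate versus delayed incentive.
- **Limitations.** Extend the existing caution about the second questionnaire to these outcomes.

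The cost is a change of wording and analysis on data already being collected. Less of the step series informs the incentive-versus-none contrast, with some loss of precision. The group-by-phase model keeps the later months in the analysis, so information on whether effects persist is not discarded.

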### Data Analysis

Due to the nested structure of the data, mixed-effect models will be used for data analysis. As measurements are nested within participants, the step count measurements represent the level 1 unit of analysis, whereas the participants represent the level 2 unit of analysis. A recent article [73] discusses the problem of faking with regard to financial incentives, (eg, faking step counts in order to qualify for financial rewards). This problem applies to our study as step counts could be entered manually. Step count measurements that are unusually high and were manually entered are likely to represent a tendency of faking. Thus, univariate and multivariate outlier analysis [74] will be conducted in order to identify participants that are prone to faking. Changes on outcomes solely measured at T_1_ and T_2_ will be analyzed performing a repeated-measures analysis of variance (rmANOVA). The analyses will be conducted using the nlme-package [75] in R [76] and the typical significance level of α = 5% will be applied.

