To avoid spill-over effects between the different incentive strategies [45], potential participants were assigned to the different groups based on their canton of residence and invitations were send out after the assignment was complete. As at the beginning of the program, the control group (CG) appeared to be the least attractive condition we wanted to contact a different number of potential participants for the 3 groups according to a proportion of 2 (EG1):2 (EG2):1 (CG/EG1). In order to do so and to further account for differences in activity preferences between urban and rural areas in Switzerland [59], cantons were grouped in blocks of 5 according to number of customers and population density. Each block contained 2 pairs of cantons that were matched for geographical proximity. The matched pairs were then randomly assigned to one of the EGs and the remaining canton was assigned to the control group. To facilitate clustering, cantons with very few customers were combined and treated as one unit. We used the approach of Gao and colleagues [60] for nonaggregate cluster-randomized controlled trials with binary outcomes to estimate the number of participants to be contacted in order to detect an expected difference in participation rate. Being conservative in comparison to public polls [53] and studies [11], we expected a difference of 5% in participation rates (8% participation was expected for both intervention groups vs 3% for the control group). As participants in our study were clustered, a potential design effect had to be considered [60]. An assumed intracluster-correlation of .01 (according to [61]) and the average cluster size of mean (M) = 925 (standard deviation [SD] = 1356) yielded a design effect of 10.24. Thus, in order for the difference in participation rates to be significant at least 15,725 customers needed to be contacted (6475 for each experimental group and 2775 for the control group). We met this requirement by directly contacting 18,638 customers via email before the beginning of the PHI.

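### The stated analysis models stop at the participant and omit the allocated canton, so nominal 5% tests of the secondary outcomes would run at roughly 11% to 13% or more

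*Protocol article*

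**What the plan says.** **Allocation.** Under Participant Acquisition and Sample, the Protocol article reports that "potential participants were assigned to the different groups based on their canton of residence". Cantons were grouped in blocks of five, and those with very few customers were merged into one unit.

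**Sample size.** The same section allows for this clustering. With an intracluster correlation (ICC) assumed at .01, "the average cluster size of mean (M) = 925 (standard deviation [SD] = 1356) yielded a design effect of 10.24", and the number of customers to contact was scaled up accordingly.

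**Analysis.** The Data Analysis section gives nesting as the reason for mixed models and then lists the levels: "the step count measurements represent the level 1 unit of analysis, whereas the participants represent the level 2 unit of analysis". Outcomes taken only at T1 and T2 go to a repeated-measures ANOVA, described without a canton or block term. For all of this, "the typical significance level of α = 5% will be applied".

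**Covariates.** Baseline Characteristics adds type of residence and subjective health as covariates for the secondary outcomes, and a separate intercept for each group.

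**Primary outcome.** Data Collection and Variables defines the participation rate. No section gives a model for comparing it between groups.

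**The concern.** When whole cantons are allocated, people in the same canton share both their group and whatever else the canton has in common. Variation between cantons is then part of the error of any group comparison. A model with only days and participants treats participants as independent and leaves that variation out, so its standard errors are too small and its tests reject too often.

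The article is not simply silent here. It names the nesting and stops one level below the unit that was allocated, although its sample size paid for that level. Type of residence (town to countryside) is a characteristic of the person's surroundings and does not identify the canton. Group-specific intercepts describe the groups, not the variation between cantons within a group. At stake are the conclusions about continued use, step counts, self-reported activity and health.

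**Working it through.** **Inputs from the article.** ICC .01, mean cluster size 925, SD 1356, expected participation 8% versus 3%, and 18,638 customers contacted (Participant Acquisition and Sample). T1 respondents 1319: 626, 562 and 131 (Survey Participation). Cantons 26: 8, 11 and 7 (Table 1). Alpha 5% (Data Analysis).

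**Assumptions.** Tests are two-sided. The ICC of .01 applies to the secondary outcomes. T1 respondents stand for active participants.

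**1. The plan's own figures.**
- Design effect = 1 + (925 − 1) × .01 = 10.24, as stated.
- With 80% power assumed and a 7:3 allocation, detecting 8% versus 3% needs 247 independent controls. 247 × 10.24 = 2529, or 2.73 clusters of 925, rounded up to 3 (2775). Each incentive group needs 6.38 clusters, rounded up to 7 (6475). The total of 6475 + 6475 + 2775 = 15,725 matches the article.

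**2. Error rate of a test that ignores clustering.** With design effect DE, a nominal 5% test has a true rate of 2 × [1 − Φ(1.96/√DE)].

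**3. Secondary outcomes among participants.**
- 26 cantons: 1319/26 = 50.7 per unit; DE = 1 + 49.7 × .01 = 1.50; rate 10.9%.
- Merged units: 18,638/925 ≈ 20 units; 1319/20 ≈ 66 per unit; DE = 1 + 65 × .01 = 1.65; rate 12.7%.
- Unequal sizes as among contacted customers: CV = 1356/925 = 1.47 and DE = 1 + [(CV² + 1)m − 1] × .01. This gives 2.59 for m = 50.7 and 3.05 for m = 65.5 (1319/20.15), with rates of 22% and 26%.
- Simulation with the reported group sizes and equal cantons within each group: 8% to 9%. The control cantons are small (131/7 ≈ 19 people each).
- Other ICCs, by the formula with equal units: .005 gives DE 1.25 to 1.32 and 8% to 9%; .02 gives 17% to 20%; .05 gives 29% to 34%.

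**4. Participation rate, if canton were ignored there too.**
- DE 10.24: 1.96/3.2 = 0.6125, rate 54%. Simulation with 7 versus 3 clusters of 925 also gives 54%.
- 26 equal cantons of 717: DE 8.16, rate 49%.
- Simulations with Table 1's canton counts and customer totals: 42% to 57%, depending on how unequal the cantons are. Fewer, very unequal units give about 60%.
- ICC of .002 instead of .01: about 25%.

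**The case against.** **A condensed article may leave the model to a fuller plan.** This holds for the participation rate. No model is stated for it, and the sample-size method was chosen for cluster-randomized trials with binary outcomes, which suggests that the authors had clustering in mind. It does not hold for the secondary outcomes, where the article itself lists the levels and leaves out the allocated one.

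**A reader might infer that the stated models carry a false-positive rate above 50%.** The documents do not support that. The design effect of 10.24 comes from 925 contacted customers per cluster, whereas the stated two-level model concerns step counts in participants, of whom there are about 51 to 66 per unit. Passing 50% there would need a design effect of about 8.4, hence an ICC of about .11 to .15. The 54% belongs only to a participation-rate comparison that ignored canton, and the article does not say that this will be done.

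**The ICC is itself an assumption.** This stands. For T1-to-T2 change, the relevant ICC is that of the change, which the article does not give and which could be smaller or larger than .01. The direction of the error does not depend on it: with any positive ICC, leaving canton out makes the tests too liberal.

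**Conclusion.** The defect is real for the analyses that the article specifies. Canton was the unit of allocation and entered the sample size, but it appears in neither the mixed models nor the repeated-measures ANOVA.

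At the plan's ICC, nominal 5% tests of the secondary outcomes would run at about 11% to 13%, and up to about 26% if participants are spread over units as unevenly as the contacted customers. The most favourable check at that ICC, equal cantons within the reported group sizes, still gives 8% to 9%. These figures rest on two-sided testing, on carrying .01 over to the secondary outcomes, and on T1 respondents as a proxy for participants.

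For the participation rate the conclusion is conditional. If that comparison ignored canton, the rate would be about 54% at the plan's design effect, and roughly 42% to 60% depending on the number and inequality of units. That the primary analysis will ignore canton is not established.

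**What to change.** - Make the allocated unit (the canton, or the merged group of small cantons) the top level of every between-group model: days within participants within canton units, and T1/T2 values within participants within canton units.
- Account for the allocation blocks in these models.
- State the analysis of the participation rate, with all contacted customers as the denominator and a method that respects canton. Either a small-sample t-based comparison of unit-level proportions or a logistic mixed model with a random canton intercept would serve.

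This changes wording and model specification and needs no new data beyond each customer's allocated unit. The price is wider confidence intervals, which reflect the number of cantons and not only the number of people. The article reports baseline results only, so the change is best fixed in writing before outcomes are analysed.

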## Discussion

### Strengths and Limitations

This study protocol describes the design and baseline characteristics of a longitudinal cluster-randomized controlled trial testing the effects of monetary and charitable incentives on the acceptance of and adherence to a pedometer-based health prevention program. To the best of our knowledge, this is the first study to systematically test the effects of different incentive strategies within a pedometer-based health intervention offered by a large health insurance company in western cultures. External validity has to be pointed out as a key strength of the described trial. Both study design and incentive strategies are tested in a real-world setting, thus ensuring the applicability of the results and conclusions.

When interpreting the results of this study, some limitations have to be considered: selection effects might affect the participation in the PHI. For example, by especially attracting highly motivated or physically active participants, those effects could potentially undermine the power of our analyses. However, we will be able to control our analyses for prior level of physical activity. Further, comparisons of T_2_ measures between the groups have to be interpreted with caution, because T_2_ reflects different time points for experimental and control groups. T_2_ was set at 6 months after start of the intervention for the EGs and at 3 months for the CG. However, the main focus of this study is on the acceptance of the promotion program, which is operationalized using the participation rate, and is thus not dependent on any T_2_ measurement. Lastly, the goal of reaching 10,000 steps per day on average might have detrimental motivational effects for some participants. It might be perceived as too challenging for very inactive participants or when participants were not able to achieve sufficiently high step counts for several days in a month.

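### For outcomes measured only at T1 and T2, the planned rmANOVA would test a 6-month change in the incentive groups against a 3-month change in control, so contrasts with control cannot isolate the incentive effect

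*Protocol article*

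**What the plan says.** Under Data Collection and Variables, T1 "is set at the beginning of the PHI for all groups", whereas T2 "is set at the end of the intervention for the experimental groups and after the first half of the intervention for the control group". The Strengths and Limitations section puts this in months: "T_2_ was set at 6 months after start of the intervention for the EGs and at 3 months for the CG". The early control measurement is deliberate, because it comes before control is rewarded. Under Experimental Groups: "Participants of the control group received no incentives over the first 3 months of the PHI". Rewards for control follow in months 4 to 6.

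For the analysis, the Data Analysis section states: "Changes on outcomes solely measured at T_1_ and T_2_ will be analyzed performing a repeated-measures analysis of variance (rmANOVA"). The significance level is 5%. No group is excluded and the unequal interval is not mentioned. For the mixed-effects models, the section names step-count measurements as level 1 and participants as level 2. It names no canton level, although Participant Acquisition and Sample describes random assignment by canton.

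The limitations section acknowledges the timing problem: "comparisons of T_2_ measures between the groups have to be interpreted with caution". It adds that the main focus, participation rate, "is thus not dependent on any T_2_ measurement".

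**The concern.** With two time points and three groups, the term of interest is the group-by-time interaction, that is, the difference between groups in mean T1-T2 change. In a contrast with control, that term is a 6-month change minus a 3-month change. Whatever happens to self-reported activity or perceived health between months 3 and 6 enters the estimate in full. This may be longer programme use, fading enthusiasm or the passage of time.

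The bias can go either way. It could create an apparent incentive effect or hide a real one. The Introduction notes that incentive effects on performance may be short-lived, so the month of measurement could matter. At stake are the questionnaire outcomes with both a T1 and a T2 value: hours of moderate to vigorous activity, hours of walking, walking to work, activity at work and in spare time, and health perception.

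**Working it through.** **1. Who is measured when**

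| Group | T1 | T2 | Interval | Rewarded between T1 and T2 |
|---|---|---|---|---|
| Financial incentive (EG1) | start | month 6 | 6 months | yes |
| Charitable incentive (EG2) | start | month 6 | 6 months | yes |
| Control | start | month 3 | 3 months | no |

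Write C(3) for the mean change from T1 to month 3 without an incentive, d for the further change from month 3 to month 6 that would occur without an incentive, and e for the incentive effect at month 6.

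- EG1 or EG2 minus control = [C(3) + d + e] - C(3) = e + d.
- EG1 minus EG2 = [C(3) + d + e1] - [C(3) + d + e2] = e1 - e2, so a d common to both groups cancels.

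The interval is 6 months for everyone in EG1 and EG2 and 3 months for everyone in control. There is no overlap from which a covariate model could estimate d. Adjusting for residence and subjective health, as the Results section plans, does not remove it.

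**2. How far an unmodelled d could move the test (illustration)**

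The plan states no power or precision for the T1-T2 analyses, so there is no figure of its own to reproduce here. The documents give no value for d either, so a range is assumed.

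Inputs: T1 survey sizes of 626 (EG1) and 131 (control) from Survey Participation; 5% level from Data Analysis, taken as two-sided. Assumptions: no true incentive effect, normal approximation, equal SD of change in both groups, clustering ignored.

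SE in SD units = sqrt(1/626 + 1/131) = 0.0961. The rejection probability is Φ(d/SE - 1.96) + Φ(-d/SE - 1.96).

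| Assumed d (SD of change) | All T1 respondents | 50% respond at T2 (assumed) |
|---|---|---|
| 0 | 5% | 5% |
| 0.05 | 8% | 7% |
| 0.1 | 18% | 11% |
| 0.2 | 55% | 31% |
| 0.3 | 88% | 60% |

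For example, at d = 0.1, d/SE = 0.1/0.0961 = 1.04, which gives 18%. With 562 (EG2) in place of 626 the result is also 18%. EG1 against EG2 stays at 5% for any common d.

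**3. In units of an outcome**

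Table 1 gives SDs for weekly hours of walking of 13.44 (EG1) and 10.87 (control). The pooled SD is sqrt[(625 × 13.44² + 130 × 10.87²)/755] = 13.03. An assumed shift of 1 hour per week is then 1/13.03 = 0.077 SD. If the SD of change equals this T1 SD (a T1-T2 correlation of 0.5), the rejection probability is about 13%. For correlations of 0.3 to 0.7 it is about 10% to 18%. With the 0.5 correlation and 50% T2 response it is about 9%. The estimate is off by the full hour in every case. The walking data are skewed and Table 1's comparison uses logs, so this is a rough scale only.

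**4. Canton**

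The sample-size section's design effect reproduces: 1 + (925 - 1) × 0.01 = 10.24. That cluster size counts customers contacted. For the survey, 1319 respondents over 26 cantons is 50.7 per canton. If the same correlation of 0.01 held for a questionnaire outcome (an assumption), the design effect would be 1 + (50.7 - 1) × 0.01 = 1.50. It would be somewhat higher in practice, since small cantons were merged into fewer units.

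**The case against.** The strongest reply is that nothing is hidden. The limitations section states the two time points, asks for caution, and notes that the primary outcome does not depend on T2. The early control T2 also has a sound reason: at month 6 control has been rewarded for three months, so there would be no unincentivised comparison left. All of this stands. It limits the point to secondary outcomes and rules out moving control's T2 as the remedy. It does not answer the point, because caution in interpretation leaves the planned 5% test and its estimate as they are.

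A reader might infer more than the documents support:

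- **That no group effect on T1-T2 outcomes may be tested.** This is too broad. EG1 and EG2 share both time points.
- **That a season effect is established.** The monthly mails carried tips for summer and for winter, but no calendar dates are given. Season is one plausible source of d, and the different length of exposure is enough for the argument.
- **That participants without T2 will be deleted.** A classical rmANOVA would do this, but the section names nlme, which can fit models that keep incomplete cases. The article does not settle it.
- **That error rates of 55% or more are to be expected.** They need shifts of 0.2 SD or more, which nothing in the documents supports.
- **That the 10.24 design effect carries over.** It belongs to the customers contacted, as shown above.

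It can also be said that clustering is a separate matter from timing. It is. It is included because the same models would be rewritten and the article states their levels explicitly.

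**Conclusion.** The concern holds for contrasts with control on outcomes measured only at T1 and T2. There, incentive and measurement time are completely aliased, which follows from the design and needs no numerical assumption. The size of the bias is unknown. Shifts of 0.05 to 0.1 SD, which are assumed, would raise the error rate from 5% to about 8% to 18% at full T1 numbers, and to 7% to 11% with half responding at T2. The figures ignore clustering.

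EG1 against EG2 on these outcomes and the participation rate are not affected. This is a disclosed limitation of secondary outcomes that the analysis section has not acted on. It should be corrected in the analysis wording, and it does not threaten the trial's main conclusion.

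**What to change.** Amend the Data Analysis section as follows:

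1. Limit inferential comparisons of T1-T2 change to EG1 against EG2.
2. Report control's change from T1 to month 3 descriptively, labelled as a 3-month change, with no test against the incentive groups.
3. Base secondary activity comparisons with control on the daily step counts of months 1 to 3. These are already collected in all groups over the same window, before control is rewarded.
4. Fit both analyses as mixed models that include the randomised canton unit (with merged small cantons as one unit) as well as participant. The nlme package already named can do this.

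The cost is analysis wording only, with no new data or payments. The downside is that the questionnaire outcomes, including health perception, lose a formal test against control. The month 1-3 step comparison removes the timing problem, but not the self-selection into the programme that the limitations section already names.
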